#### 4.3.1 Cervical HPV infections

- **Incident cervical HPV infection:** an incident cervical infection with a given HPV type is defined as the new detection of this HPV type (by PCR) at any time point during the follow-up period (i.e. after enrolment in the control arm of study HPV-008).
- **Transient cervical HPV infection:** a transient cervical infection with a given HPV type is defined as the detection of this HPV type (by PCR) at any single time point during the follow-up period followed by a negative sample for that HPV type at the evaluation performed 6 months after the evaluation when the cervical HPV infection was first detected.
- **6-month persistent cervical HPV infection:** a persistent cervical HPV infection (6-month definition) is defined as the detection of the same HPV type (by PCR) in cervical samples at two consecutive evaluations over approximately a 6-month interval. Thus, the algorithmic definition of a 6-month persistent infection is that there exists a sequence of positive samples with the same HPV type, not interrupted by negative samples, such that the total range is more than 5 months ( $> 150$  days). The start of the persistent cervical HPV infection is defined as the date of the first positive sample in the sequence.
- **12-month persistent cervical HPV infection:** a persistent cervical HPV infection (12-month definition) is defined as the detection of the same HPV type (by PCR) at all available time points over approximately a 12-month interval. Thus, the algorithmic definition of a 12-month persistent cervical infection is that there exists a sequence of positive samples with the same HPV type, not interrupted by negative samples, such that the total range is more than 10 months ( $> 300$  days). The start of the persistent cervical HPV infection is defined as the date of the first positive sample in the sequence.
- **Other cervical HPV infection:** other cervical HPV infections than those described above will be considered in the analysis. These infections are cervical HPV infections with duration less than 150 days and cervical HPV infections detected at the last visit and for which it is not possible to determine if they are transient or persistent.

- **Clearance of cervical HPV infection:** two definitions will be used:

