### 4.4.2 Clinical determinants

For each reference cervical HPV infection with a given HPV type over the 48-month follow-period, the following determinants will be defined:

- HPV type: 16; 18; 31; 33; 45; Other high risk HPV type; Other low risk HPV type.

The above categorization of HPV types will be used in the univariate and multivariable analyses. All HPV types will be considered individually in the tables presenting descriptive statistics by HPV type as well as high risk and low risk categories. The high risk (oncogenic) category is obtained by grouping together HPV types 16, 18, 31, 33, 35, 39, 45, 51, 52, 56, 58, 59, 66, and 68. The low risk (non-oncogenic) category is obtained by grouping together HPV types 6, 11, 34, 40, 42, 43, 44, 53, 54, 70 and 74. In some cases, the category “No cervical HPV infection” will be added in the categorization for univariate and multivariable analyses.

- HPV infection category: 6-month persistent, less than 6-month persistent, transient, last visit detected.
- Previous cervical HPV infection: No; Yes, with at least one high risk HPV type; Yes, with only low risk HPV type.
- Histopathologically-confirmed CIN2+ (or CIN1+, or CIN3+) following the reference cervical HPV infection, associated with a different HPV type, and preceding the CIN2+ (or CIN1+, or CIN3+) associated with the same HPV type as the reference infection (i.e. date of CIN2+ (or CIN1+, or CIN3+) following the reference infection strictly inferior to date of CIN2+ (or CIN1+, or CIN3+) associated with the same HPV type as the reference infection): No; Yes, with at least one high risk HPV type; Yes, with only low risk HPV type.

- Histopathologically-confirmed CIN2+ (or CIN1+, or CIN3+) preceding the reference cervical HPV infection, associated with a different HPV type : No; Yes, with at least one high risk HPV type; Yes, with only low risk HPV type.
- Co-infection with other HPV types (concomitant cervical HPV infections): No; Yes, with at least one high risk HPV type; Yes, with only low risk HPV type.

Co-infection with other HPV types is defined as the detection of these HPV types at time of the onset of the reference cervical HPV infection or, if this infection is persistent, during the duration of the reference cervical HPV infection until its end or until the occurrence of the event, whichever comes first.

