#### 6.2.4.5 Statistical methods

The time between persistent cervical HPV infections and lesions will be analyzed using Kaplan-Meier method and Cox regression models.

Kaplan-Meier curves presenting the cumulative probability of lesions following 6-month persistent cervical HPV infections will be displayed and compared between groups for determinants of interest using the Log-rank test (univariate analyses). Cox regression models will be also performed for the univariate analyses in order to obtain unadjusted hazards ratios of the determinants of interest.

In addition, a multivariable Cox regression model will be performed in order to estimate the relative contribution of each determinant adjusting for the simultaneous effects of the other covariates. The model will include: time-independent covariates (e.g., age and region at study entry), time-independent covariates re-assessed at follow-up visits (e.g., behavioral determinants updated over the follow-up period using the yearly behavioral questionnaires) and time-dependent covariates (e.g., concomitant cervical HPV infections, i.e. co-infection). Also, some of the determinants will be distinguished depending on whether they started

before or after the 6-month persistent cervical HPV infections leading to the lesions in order to differentiate their effects in the pathway leading from cervical HPV infection to lesion (cf. Sections 4.4.2 and 4.4.3 for the definition of behavioral and clinical determinants and Section 8.5.1 for the list of determinants that will be taken into account in the analysis).

As the same subject may contribute to more than one observation (e.g., the same women may have several persistent cervical HPV infections of same or different HPV types leading or not to lesions associated with these HPV types), the analysis will be performed using an appropriate approach (counting process, clustering etc.) carried out either by a standard or a stratified Cox model depending on whether i) the recurrent events may be considered as identical or different and ii) the assumption that the estimated proportional hazards are constant over time is fulfilled or not [Andersen et al., 1993; Prentice et al, 1981; Kelly and Lim, 2000; Kleinbaum and Klein, 2005].

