#### 6.2.5.4 Time computation

The time between the onset of a cervical HPV infection (any HPV infection) and a histopathologically-confirmed CIN2+ (or CIN1+, or CIN3+) associated with the same HPV type will be calculated in days as: Date of event or Date of censoring - Date of detection of the cervical HPV infection.

The date of event will be:

- the date of the detection of the histopathologically-confirmed CIN2+ (or CIN1+, or CIN3+) associated with the same HPV type as the HPV type of the cervical HPV infection,

The date of censoring will be:

- the date of Month 48 visit for subjects who attended all visits during the 48-month follow-up period and who had a histopathologically-confirmed CIN2+ (or CIN1+, or CIN3+) not associated with the same HPV type as the cervical HPV infection or who did not have a histopathologically-confirmed CIN2+ (or CIN1+, or CIN3+) or during this period,
- the date of the last PCR reported at the latest visit for which data are available or the date of the last cytology or the date of the last biopsy (if the date is after the date of the last PCR) for subjects who did not attend all visits during the 48-month follow-up period and who had a histopathologically-confirmed CIN2+ (or CIN1+, or CIN3+) not associated with the same HPV type as the cervical HPV infection or who did not have a

histopathologically-confirmed CIN2+ (or CIN1+, or CIN3+) throughout their follow-up period (from first to last visit).

- Special cases:
  - In case two distinct cervical HPV infections (i.e. separated by a clearance) associated with the same HPV type are detected for a same subject and a histopathologically-confirmed CIN2+ (or CIN1+, or CIN3+) associated with this HPV type is detected after the second infection, the date of censoring of the first infection will be the date of onset of the second infection since the event (i.e. detection of a histopathologically-confirmed CIN2+ (or CIN1+, or CIN3+)) is associated with the second detected infection (in chronological order).

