### 6.2.5.5 Statistical methods

The time between any cervical HPV infections and lesions will be analyzed using the same models and methodology as for the analysis of the time between persistent cervical HPV infections and lesions (cf. Section 6.2.4.5).

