## 9.5 Determinants taken into account in the analyses

### 9.5.1 Analysis of time between persistent (or any) cervical HPV infections and lesions

|                                                           | Covariates                                      | Type    | Categories                                                                                                                                                                             | Time-dependent | Comment                      |
|-----------------------------------------------------------|-------------------------------------------------|---------|----------------------------------------------------------------------------------------------------------------------------------------------------------------------------------------|----------------|------------------------------|
| Main covariate                                            | HPV type                                        | Class   | HPV 16
HVP 18
HPV 31
HVP 33
HPV 45
Other high risk HPV type (35, 39, 51, 52, 56, 58, 59, 66, 68)
Other low risk HPV type (6,11, 34, 40, 42, 43, 44, 53, 54, 70, 74 ) | No             | Main variable of interest    |
| Demographic characteristics
(defined at subject level) | Region                                          | Class   | Europe
Asia Pacific
Latin America
North America                                                                                                                               | No             |                              |
| Behavioral Covariates
(defined at subject level)       | Smoking                                         | Ordinal | [0-0.5[ pack/year
≥0.5 pack/year                                                                                                                                                    | No             | Re-assessed at yearly visits |
|                                                           | Age at beginning of sexual activity (years)     | Ordinal | Never had sexual intercourse
<15
15-17
18-25                                                                                                                                  | No             |                              |

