|                     | Intra-uterine device                                                                                                                                                                                                                              | Binary | No
Yes                                                                              | No             | Re-assessed at each visit |
|                     | Sterilized                                                                                                                                                                                                                                        | Binary | No
Yes                                                                              | No             | Re-assessed at each visit |
|                     | Chlamydia trachomatis                                                                                                                                                                                                                      | Binary | No
Yes                                                                              | No             | Re-assessed at each visit |
| Clinical covariates | HPV infection category §                                                                                                                                                                                                                          | Class  | 6-month persistent
Less than 6-month persistent
Transient
Last visit detected | No             |                           |
|                     | Previous cervical HPV infection                                                                                                                                                                                                            | Class  | No
Yes, with at least one high risk HPV type
Yes, with only low risk HPV type    | No             | Re-assessed at each visit |
|                     | Histopathologically-confirmed CIN1+ following the reference cervical HPV infection, associated with a different HPV type, and preceding the CIN2+ (or CIN1+, or CIN3+) associated with the same HPV type as the reference infection | Class  | No
Yes, with at least one high risk HPV type
Yes, with only low risk HPV type    | Yes            | Re-assessed at each visit |

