|                     | Histopathologically-confirmed CIN1+ preceding the reference cervical HPV infection, associated with a different HPV type                                                                                                                   | Class  | No
Yes, with at least one high risk HPV type
Yes, with only low risk HPV type    | No             | Re-assessed at each visit |
|                     | Co-infection* with other HPV types (concomitant cervical HPV infection)                                                                                                                                                                    | Class  | No
Yes, with at least one high risk HPV type
Yes, with only low risk HPV type    | Yes            | Re-assessed at each visit |

\$ Only for the analysis of time between any cervical HPV infections and lesions.

\* Co-infection with other HPV types is defined as the detection of these HPV types at time of the onset of the reference cervical HPV infection or, if this infection is persistent, during the duration of the reference cervical HPV infection until its end or until the occurrence of the event, whichever comes first.

Consequently any cervical HPV infection which onset is prior to the onset of the reference cervical HPV infection will be considered as a previous cervical HPV infection and any cervical infection which onset if after the end of the reference cervical HPV infection and before the occurrence of the event will not be considered as a co-infection.

However, when analyzed as time-varying covariables, co-infections will be considered until the occurrence of the event (e.g., lesion).

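### In the any-infection lesion models, the multivariable HPV-type hazard ratio is adjusted for infection category, which is determined after onset and lies on the path from type to lesion

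*SAP*

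**What the plan says.** - SAP 9.5.1 gives one covariate table for the persistent-infection and any-infection lesion analyses. HPV type is the main covariate, with the comment "Main variable of interest".
- The same table lists "HPV infection category" among the clinical covariates, marked as not time-dependent. Its footnote reads "Only for the analysis of time between any cervical HPV infections and lesions".
- SAP 4.4.2 gives the levels: "HPV infection category: 6-month persistent, less than 6-month persistent, transient, last visit detected".
- SAP 6.2.5.5 states that the any-infection analyses "will be analyzed using the same models and methodology as for the analysis of the time between persistent cervical HPV infections and lesions". That model, in 6.2.4.5, is a multivariable Cox regression meant to "estimate the relative contribution of each determinant adjusting for the simultaneous effects of the other covariates".
- SAP 6.2.5.4 measures time as "Date of event or Date of censoring - Date of detection of the cervical HPV infection".
- SAP 4.3.1 defines 6-month persistence by an uninterrupted run of positive samples "such that the total range is more than 5 months" (over 150 days), and transience by a negative sample at the evaluation 6 months later.

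**The concern.** The clock starts when the infection is first detected. Whether that infection is persistent or transient is known only from later samples. Infection category is therefore a post-onset variable and cannot be a common cause of HPV type and lesion.

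The SAP treats both links of a pathway as plausible. HPV type is the main covariate in the clearance models (9.5.2), and the primary objective takes persistent infection as the stage before CIN2+ (2.1). If both links hold, infection category is an intermediate, and conditioning on it takes out the part of the type effect that passes through it. Coding the category correctly in time would not change this.

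The hazard ratios at stake are those for HPV type in three secondary objectives: CIN1+, CIN2+ and CIN3+ after any infection. A ratio conditional on persistence answers a question close to the one in 6.2.4, where all infections are already 6-month persistent. The lesion hazard after infection with a given type, adjusted for region and behaviour but not for what the infection later does, would not be reported.

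**Working it through.** **1. Is the adjusted model the only multivariable one planned?** Section 9.5.1 lists infection category without condition, and 6.2.5.5 carries over a model in which each determinant is adjusted for the others. No section specifies a multivariable any-infection model without the category. Univariate Cox models are planned (6.2.4.5), but they adjust for nothing.

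**2. Is the category downstream of type?** Time origin: first detection (6.2.5.4). Category: from samples up to and beyond 150 days later (4.3.1). It is fixed after the origin.

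**3. Size.** The SAP states no figure on this point and gives no persistence or progression rates by type, so every input here is an assumption:
- direct type hazard ratio d = 2;
- lesion hazard ratio for persistent against non-persistent infection h = 3, 5 or 10;
- probability of persistence p1 for the index type and p0 for the comparison types.

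With rare events, full hazard ratio = d × [1 + p1(h − 1)] / [1 + p0(h − 1)].

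| p1 v p0 | h = 3 | h = 5 | h = 10 |
|---|---|---|---|
| 50% v 40% | 2 × 2.0/1.8 = 2.22 | 2 × 3.0/2.6 = 2.31 | 2 × 5.5/4.6 = 2.39 |
| 60% v 35% | 2 × 2.2/1.7 = 2.59 | 2 × 3.4/2.4 = 2.83 | 2 × 6.4/4.15 = 3.08 |
| 70% v 30% | 2 × 2.4/1.6 = 3.00 | 2 × 3.8/2.2 = 3.45 | 2 × 7.3/3.7 = 3.95 (3.946) |

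A model that conditions fully on persistence returns about d = 2 in every cell. On the log scale the share left out runs from 1 − ln 2/ln 2.22 = 13% to 1 − ln 2/ln 3.946 = 50%.

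**4. Check by simulated Cox fits** (60,000 infections per run, mean of 8 runs, index type in 20%, persistence as a yes/no category):

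| p1 v p0, h, d | Without category | With category |
|---|---|---|
| 60% v 40%, 5, 2 | 2.62 | 2.02 |
| 60% v 30%, 10, 2 | 3.43 | 1.99 |
| 60% v 40%, 5, 1 | 1.38 | 1.04 |
| 50% v 50%, 5, 2 | 2.03 | 2.03 |

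The last row is the null case: if persistence does not differ by type, nothing is lost.

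**5. Is all of the persistence effect removed?** No. The 6-month persistent level pools every duration over 150 days. Letting longer persistence also depend on type and raise the hazard (60% v 40%, h = 5, d = 1) gave 1.54 without the category and 1.13 with it. Part of the persistence effect stays in the type ratio.

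**6. Direction.** If the direct and persistence effects oppose each other, adjustment can move the ratio away from 1. With a direct ratio of 0.6 and a persistence factor of 1.4, the full ratio is 0.6 × 1.4 = 0.84, and the adjusted ratio is 0.6.

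**The case against.** The best defence is that the SAP never promises a total effect. Its objectives are to describe and evaluate determinants, infection category is one of those determinants (4.4.2), and 6.2.4.5 says openly that each is adjusted for the others. A type hazard ratio conditional on category is what such a model delivers. This stands as a description of the model. It does not settle the matter, because nowhere is the type ratio labelled as conditional on persistence, and type is the variable singled out as of main interest.

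Second, the unconditional effect is partly visible elsewhere: Kaplan-Meier curves, log-rank tests and unadjusted hazard ratios (6.2.4.5), endpoint descriptions stratified by type (6.2.3.1), and the clearance models. This also stands, and narrows the gap to a confounder-adjusted effect from onset. The documents do not show how strongly region or behaviour confound type, so the gap may be small or large.

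Third, model content is not fully locked. Inclusion depends on a determinant's meaning for the endpoint, changes in point estimates inform interpretation (6.1.2), and AIC, SBC and consistency guide model choice (6.2.4.5). None of these guarantees a model without the category. Fit criteria tend to keep a strong predictor, and the rule in 6.2.5.3 that links a lesion first to a 6-month persistent infection makes the category a stronger one.

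A reader might go further and infer that the adjusted ratio is always too close to 1, or that the whole persistence effect disappears. The documents support neither. Section 9.5.1 names no reference type and no direction for any direct effect, and the pooled durations leave part of the persistence effect in place.

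**Conclusion.** The point holds for the multivariable any-infection analyses of CIN1+, CIN2+ and CIN3+. It is conditional on persistence differing by HPV type and affecting lesion risk; if either fails, nothing is lost. Where both hold, the planned type hazard ratio omits most, not all, of the effect acting through persistence. It moves toward 1 when the direct and persistence effects agree in direction, and may move away from 1 when they do not.

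Under the assumed inputs, a full hazard ratio of 2.2 to 3.9 would be reported as about 2. These figures illustrate the mechanism and are not estimates for this study.

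It would be wrong to infer that the primary result is at risk. The primary analysis and the other persistent-infection analyses do not carry this covariate. The change is worth making because the affected ratio concerns the variable of main interest in three secondary objectives and the remedy is cheap.

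**What to change.** In 6.2.5.5 and 9.5.1, for the any-infection analyses:

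- Take the reported HPV-type hazard ratios from a multivariable model without infection category, using covariates known at infection onset: region, age, behavioural and CRF determinants, previous infection, preceding CIN, and co-infection present at onset.
- Keep the model with infection category as a second analysis for that determinant, and label its type hazard ratio as conditional on infection category.

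The cost is SAP wording and one extra model per lesion endpoint, three in all, with no new data. Co-infection at onset has to be separated from co-infection appearing later, because the 4.4.2 definition covers both.
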